**Figure 2 F2:**
[figure not shown]
**Plantar fascia thickness: example of measurement location**.

### Secondary outcomes

Secondary outcomes will be function, use of oral analgesic medication, and 'first-step' pain at 4, 8 and 12 weeks. Function will be measured by the foot function domain of the FHSQ, which has been shown to have a high degree of internal consistency (Cronbach's α = 0.85) and test-retest reliability (intra-class correlation coefficient = 0.92) [33]. Participants treated for bilateral plantar fasciitis will be asked to describe foot function without specific reference to an individual foot (i.e. bilateral function will be evaluated as one independent sample). Use of oral analgesic medication (including paracetamol, aspirin, opioids and non-steroidal anti-inflammatory drugs) will be recorded at each visit. 'First-step' pain, experienced when initially rising from bed in the morning, will be measured on a 100 mm visual analogue scale. Participants treated for bilateral plantar fasciitis will be asked to indicate the magnitude of symptoms without specific reference to an individual foot (i.e. bilateral pain will be evaluated as one independent sample).

### Sample size

Prospective sample size calculation indicates a sample of 40 participants per group (i.e. 80 total) would provide 80% power to detect a minimal important difference of 13 points [35] on the pain domain of the FHSQ (SD = 20, alpha = 0.05, 5% loss to follow-up). The extra precision provided by covariate analysis was conservatively ignored when performing this calculation.

### Adverse events

Complications and adverse events associated with the intervention (e.g. infection, nerve injury or plantar fascia rupture) will be recorded in participant files and reported in the final manuscript.

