### Interventions

Participants will be randomly allocated to one of two treatment arms: (i) ultrasound-guided injection of the plantar fascia with corticosteroid (experimental group), or (ii) ultrasound-guided injection of the plantar fascia with normal saline (control group). Prior to plantar fascia injection, participants in both groups will be given an ultrasound-guided posterior tibial nerve block with 2% lignocaine hydrochloride. All participants will be positioned prone on a treatment table with their knees extended. Corticosteroid injection will be performed with a 25 gauge (38 mm) needle and a 1 mL Luer-lock syringe containing 1 mL of 4 mg/mL dexamethasone sodium phosphate. Saline injection will be performed with a 25 gauge (38 mm) needle and a 1 mL Luer-lock syringe containing 1 mL normal saline (0.9% sodium chloride). For both injections, the needle will be inserted through the medial heel perpendicular to the long axis of the ultrasound transducer, and will be advanced under continuous guidance into the proximal plantar fascia [31]. Infiltration will occur near the calcaneal enthesis in the region of maximal fascia thickening. An aseptic technique will be used for all injections to minimise infection risk, including use of sterile gloves, sterile transducer covers and sterile transmission gel. Participants with bilateral plantar fasciitis will have both feet treated (with their allocated intervention) during a single appointment. Following treatment, participants will be advised to avoid all running and other high impact activities for at least 2 weeks.

Throughout the initial 8 weeks of enrolment, all participants will be required to complete a daily stretching program shown to decrease pain associated with plantar fasciitis [32]. The stretching technique requires participants to cross their affected leg over the contralateral knee in a seated position, then pull back on the toes until they feel a stretch in the arch of their foot. Participants will be instructed to repeat the stretch 10 times, with each stretch lasting for 10 seconds. All participants will be asked to complete the stretching program three times per day and to record their stretching frequency in a diary.

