### Randomisation, treatment allocation and blinding

Treatment allocation will be performed according to a computer-generated randomised number sequence. Allocation will be concealed in a password protected computer file accessible by an investigator not involved in measuring outcomes ([name]). This investigator will also prepare the syringe prior to heel injection, thereby ensuring the investigator giving injections, measuring outcomes and analysing data ([name]) is blinded throughout the trial duration. As both treatment solutions (i.e. dexamethasone sodium phosphate and normal saline) appear in the syringe as clear liquids free from visible particulate matter, the syringe contents will not require masking. This protocol will also ensure that trial participants are blinded to their treatment allocation.

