### Primary outcomes

Primary outcomes will be pain and plantar fascia thickness at 4, 8 and 12 weeks. Pain will be measured by the foot pain domain of the Foot Health Status Questionnaire (FHSQ), which has been shown to have a high degree of internal consistency (Cronbach's α = 0.88) and test-retest reliability (intra-class correlation coefficient = 0.86) [33]. Participants treated for bilateral plantar fasciitis will be asked to describe symptoms without specific reference to an individual foot (i.e. bilateral pain will be evaluated as one independent sample). Plantar fascia thickness will be measured by ultrasound at a standard location where the fascia crosses the anterior aspect of the inferior calcaneal border (Figure 2). This measurement technique has been shown to have good intra-rater reliability, with the 95% limits of agreement ranging from -0.7 mm to 0.5 mm [34]. Participants treated for bilateral plantar fasciitis will have thickness measurements taken for each individual foot. However, for bilateral cases, the mean change in plantar fascia thickness for the two feet will be calculated at each follow-up in order to evaluate data as one independent sample. Plantar fascia measurements and ultrasound guided injections will be performed with a variable frequency (5-10 MHz) linear array transducer (Acuson Aspen, Siemens Medical Solutions, Pennsylvania, USA).

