### Data analysis

Statistical analyses will be undertaken using SPSS software (version 14.0 or later, SPSS Corporation, Chicago, IL, USA). Continuous data will be explored for normality using standard tests to satisfy the assumptions of parametric statistics. All analyses will be conducted on an intention-to-treat basis and missing follow-up data will be replaced with baseline observations carried forward (BOCF) (i.e. baseline data will be carried forward in circumstances where follow-up observations are missing). In comparison to a last observation carried forward (LOCF) approach, BOCF has been shown to provide a more conservative estimate when analysing the treatment effect of pain-relief medication [36]. Continuous outcomes with a normal distribution will be analysed using a linear regression technique with baseline measurements adjusted for by the analysis of covariance model (ANCOVA) [37]. If data is found to be not normally distributed, transformation will be attempted. However, if data is still not normally distributed after transformation, non-parametric statistical tests will be used. Other data (nominal or ordinal) will be analysed using appropriate non-parametric statistical tests. Statistical significance for hypothesis tests will be set at the conventional level of 0.05.

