### Choice of corticosteroid

Selection of a particular corticosteroid agent for local injection varies across disciplines [43] and geographic regions [44], with limited evidence available to assist in decision-making. In relation to treatment outcomes, systematic reviews of randomised trial data have revealed no difference in clinical efficacy between various corticosteroid types [45,46]. Nonetheless, when selecting a corticosteroid for treatment of soft tissue disorders, guidelines in the rheumatology literature recommend use of an agent with high tissue solubility [42], and avoidance of fluorinated compounds [47]. When corticosteroids are injected locally, duration of action is inversely related to solubility, with high solubility agents (phosphates) having a shorter duration of action, and low solubility agents (acetates) a longer duration of action [42,48]. Accordingly, high solubility corticosteroids (e.g. dexamethasone phosphate) are thought to reduce the risk of post-injection flare and soft -tissue atrophy [49,50].

Fluorination of a corticosteroid molecule improves anti-inflammatory (glucocorticoid) action and decreases sodium retaining (mineralocorticoid) activity, thereby improving the anti-inflammatory potency of the drug while reducing systemic side effects [51]. Despite these advantages, comparisons of fluorinated versus non-fluorinated corticosteroids have demonstrated various effects by which fluorinated agents increase collagen degradation [52-54]. In addition, case-series reports of adverse events following corticosteroid injection, such as rupture of the plantar fascia, have largely involved the fluorinated corticosteroid triamcinolone [55,56]. However, this drug is also the most insoluble (and therefore longest acting) injectable corticosteroid available [48,57], and adverse events following use of shorter-acting fluorinated agents are less frequently reported. With this in mind, it is likely that injection of a corticosteroid that is both fluorinated and relatively insoluble should be avoided when treating soft tissue disorders.

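### The adverse event rule makes association with the intervention a condition for recording, which can lose events in a blinded, saline-controlled trial

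*Protocol article*

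**What the plan says.** The Adverse events section is a single sentence. Its recording rule reads "Complications and adverse events associated with the intervention (e.g. infection, nerve injury or plantar fascia rupture) will be recorded in participant files", and the sentence goes on to promise that these events will also appear in the final manuscript. It does not say who decides whether an event is associated, or by what criterion.

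Three other parts of the protocol article bear on this:

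- **Interventions.** Procedural exposure is common to the arms: "participants in both groups will be given an ultrasound-guided posterior tibial nerve block with 2% lignocaine hydrochloride". Both arms then have a 1 mL heel injection with the same needle and approach. Only the syringe contents differ.
- **Randomisation, treatment allocation and blinding.** One blinded person fills several roles, the allocation procedure "ensuring the investigator giving injections, measuring outcomes and analysing data" being kept from knowledge of treatment throughout. Participants are blinded as well: "This protocol will also ensure that trial participants are blinded to their treatment allocation".
- **Data analysis.** There is a general rule for categorical data, "Other data (nominal or ordinal) will be analysed using appropriate non-parametric statistical tests", which does not mention adverse events.

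**The concern.** In a randomised comparison that shares every procedure except the drug, the contrast between arms is what shows which harms the drug causes. A relatedness condition at the point of entry puts an opinion ahead of that contrast. Blinding makes the opinion even-handed but not informed. An assessor who does not know the allocation cannot tell whether a rise in heel pain after the visit is due to dexamethasone, the needle, the nerve block or the condition itself.

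This is a stated rule about which data will exist, so it differs from a detail that may be left to an analysis plan. An analysis plan can add tables, but it cannot restore events that were never written down.

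The protocol's own reasoning gives harms some weight. The Choice of corticosteroid section discusses flare, soft-tissue atrophy, collagen degradation and fascia rupture when selecting the agent. The Conclusion says the findings will feed recommendations on using corticosteroid injection.

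**Working it through.** **The plan's own figure.** The document gives no figure for harms, so there is none to reproduce. The group size that governs any harms comparison does reproduce. With a difference of 13, SD 20, two-sided alpha 0.05 and 80% power, n = 2 × (1.96 + 0.84)² × 20² / 13² ≈ 37.2, rounded up to 38 per group. Allowing for 5% loss, 38 / 0.95 = 40 per group. This point does not touch that calculation.

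**Reading the rule.** Two readings are open.

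1. Someone judges, event by event, whether it was associated with the intervention.
2. The phrase loosely means events that follow the procedure.

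The two readings produce different datasets from the same participants. Under either one, no sentence in the article provides for recording an event that is thought unrelated.

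**What an even-handed but uninformed filter does.** The rates below are assumptions, not document figures. Take true risks of 30% (steroid) and 10% (saline), 40 participants per arm, and a filter that keeps a share s of events equally in both arms. The expected counts are 40 × 0.30 × s and 40 × 0.10 × s. Power is for a two-sided Fisher's exact test at 0.05.

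| s | Expected events, steroid v saline | Risk difference | Risk ratio | Power |
|---|---|---|---|---|
| 1 | 12 v 4 | 20 points | 3 | 0.53 |
| 0.75 | 9 v 3 | 15 points | 3 | 0.37 |
| 0.5 | 6 v 2 | 10 points | 3 | 0.18 |
| 0.25 | 3 v 1 | 5 points | 3 | 0.03 |

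The absolute difference shrinks in proportion to s, while the expected ratio stays at 3. The loss is one of ascertainment and sensitivity.

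**What an accurate filter would do.** Under the same assumptions, suppose the 10% seen with saline is background present in both arms, and the filter removes exactly those events. The risks become 30% − 10% = 20% and 10% − 10% = 0%. The expected counts become 8 v 0, and power rises to 0.84. So a filter does not always reduce sensitivity; the result depends on how well the assessor can attribute events. In this design the assessor lacks the information that accurate attribution needs, so the first table is the more relevant guide.

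**A figure that does not measure the defect.** No events in 40 participants leaves a two-sided 95% upper limit of 1 − 0.025^(1/40) = 8.8% (one-sided, 1 − 0.05^(1/40) = 7.2%). This follows from the group size and is the same whether or not the recording rule changes. It shows only that there are few events to spare.

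**The case against.** The strongest reply is that the sentence does not use words such as only or judged, sets no causality test, and may simply mean events around the procedure. That is a fair reading. It does not remove the point, because wording that supports two datasets should be tightened, and no other section provides for all-cause recording.

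A second reply is that collection forms and tabulation belong in the full protocol or analysis plan, which are not shown. This stands for the wording of questions, table layout and confidence intervals, whose absence is no finding. It does not cover a stated condition on what is recorded.

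A reader might infer four stronger things that the document does not support:

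- **That harms will not be compared between arms.** The same sentence says events "will be recorded in participant files and reported in the final manuscript". Nothing rules out reporting by arm, and the general rule for nominal data could cover a test.
- **That flare and atrophy are left out.** The named events are examples. The Choice of corticosteroid section says high-solubility agents "are thought to reduce the risk of post-injection flare" and tissue atrophy, so these would naturally count as events associated with an injection.
- **That the harms comparison is biased between arms.** The participants and the likely assessor are blinded and both arms undergo the same procedures, so a filter should act alike in each. Differential bias is not shown.
- **That rupture will be missed because the scan is not used to look for it.** The Primary outcomes section describes how thickness is measured: "Plantar fascia thickness will be measured by ultrasound at a standard location". Its silence on fascia continuity is not a stated defect.

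**Conclusion.** The point holds in a limited form and is of minor severity. As written, the rule ties the recording of adverse events to their association with the intervention, in a design where the blinded assessor is poorly placed to judge that. It can therefore lose events and lower sensitivity to a difference in harms.

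This rests on two assumptions: that the phrase is applied as an entry condition, and that attribution is imperfect. The size cannot be estimated from the document, and the power figures above depend entirely on assumed event rates and retention shares. Harms are neither a primary nor a secondary outcome, and the primary analysis, alpha level and sample size are unaffected.

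**What to change.** Reword the Adverse events section so that:

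- all adverse events are recorded regardless of presumed cause;
- they are asked about in the same way for every participant at the existing 4-, 8- and 12-week visits, where analgesic use is already recorded;
- relatedness is kept as a separate field, completed while blinded, and is not a condition of entry;
- the number of participants with events is reported by arm.

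Optionally, fascia continuity (rupture yes or no) could be noted on the ultrasound scan already performed at each follow-up.

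The cost is a line on the visit form and, if the option is taken, a tick-box on the scan record. No extra visit, staff or procedure is needed. The downside is some unrelated minor events to tabulate. Where relatedness judgements prove informative, the separate field still allows the narrower set of events to be shown.

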### Data analysis

Statistical analyses will be undertaken using SPSS software (version 14.0 or later, SPSS Corporation, Chicago, IL, USA). Continuous data will be explored for normality using standard tests to satisfy the assumptions of parametric statistics. All analyses will be conducted on an intention-to-treat basis and missing follow-up data will be replaced with baseline observations carried forward (BOCF) (i.e. baseline data will be carried forward in circumstances where follow-up observations are missing). In comparison to a last observation carried forward (LOCF) approach, BOCF has been shown to provide a more conservative estimate when analysing the treatment effect of pain-relief medication [36]. Continuous outcomes with a normal distribution will be analysed using a linear regression technique with baseline measurements adjusted for by the analysis of covariance model (ANCOVA) [37]. If data is found to be not normally distributed, transformation will be attempted. However, if data is still not normally distributed after transformation, non-parametric statistical tests will be used. Other data (nominal or ordinal) will be analysed using appropriate non-parametric statistical tests. Statistical significance for hypothesis tests will be set at the conventional level of 0.05.

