### Setting and eligibility criteria

The trial will be conducted at the La Trobe University Podiatry Clinic and will recruit local community-dwelling participants by multiple newspaper advertisements. Participants will be required to have a clinical history of pain beneath the heel for at least eight weeks prior to enrolment, and to report a minimum heel pain magnitude of 20 mm on a 100 mm visual analogue pain scale. On clinical examination, participants will also be required to report sensitivity to palpation of the medial calcaneal tubercle and/or the proximal plantar fascia. To confirm the diagnosis of plantar fasciitis, the dorso-plantar thickness of the plantar fascia will be measured by ultrasound at a standard location where the fascia crosses the anterior aspect of the inferior calcaneal border. Participants will be required to have a plantar fascia thickness value of 4.0 mm or greater [28]. Finally, participants will be required to attend the second visit (during which a tibial nerve block and heel injection will be given) with a friend or family member who is able to provide transportation from the clinic.

Applicants will be excluded from the study if they have received a corticosteroid injection for plantar fasciitis within the previous six months, or if they have any of the following: a known hypersensitivity to lignocaine hydrochloride or corticosteroids, current skin or soft tissue infection near the injection site, posterior heel pain, current pregnancy, systemic inflammatory disease, diabetes mellitus, previous local surgery, or a history of local trauma. Applicants will also be excluded if they are unable to walk household distances without the use of an aid, or if they have commenced any treatment regimen for plantar fasciitis within four weeks prior to enrolment.

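### A normality test on the outcome data, which ANCOVA does not need, decides whether each primary result stays baseline-adjusted and on its original scale

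*Protocol article*

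**What the plan says.** The Data analysis section sets out a sequence of three methods, entered through a test: "Continuous data will be explored for normality using standard tests to satisfy the assumptions of parametric statistics". The first method applies only if the test is passed: "Continuous outcomes with a normal distribution will be analysed using a linear regression technique with baseline measurements adjusted for by the analysis of covariance model". The second follows a failure: "If data is found to be not normally distributed, transformation will be attempted". The third follows a second failure: "if data is still not normally distributed after transformation, non-parametric statistical tests will be used". Neither the transformation nor the non-parametric test is named, and baseline adjustment is mentioned only for the first method.

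The rule covers all continuous outcomes, so it governs the primary ones: "Primary outcomes will be pain and plantar fascia thickness at 4, 8 and 12 weeks". The Sample size section works in raw score units: 40 per group "would provide 80% power to detect a minimal important difference of 13 points" on FHSQ pain. It adds that no credit was taken for covariate adjustment.

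**The concern.** As written, the condition falls on the data or the outcome. The distributional assumption of ANCOVA concerns the residuals, and in samples of this size even that matters little for a test of a mean difference. A failed normality test is therefore a poor reason to abandon the model.

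Three things are at stake:

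- **Scale.** A difference on a transformed scale cannot be read directly against 13 FHSQ points, and a standard rank test gives no mean difference. For thickness, the unit lost is the millimetre.
- **Adjustment.** An ANCOVA on transformed data keeps the baseline covariate. An ordinary two-sample rank test on follow-up scores does not.
- **Consistency.** The article does not say whether the rule is applied per outcome or per visit. If per visit, weeks 4, 8 and 12 of one outcome could be reported with different methods and effect measures.

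**Working it through.** **1. The plan's own figure.** Inputs from Sample size: difference 13, SD 20, alpha 0.05 (two-sided assumed), power 80%, 5% loss.

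n per arm = 2 × (1.96 + 0.8416)² × 20² / 13² = 37.15, rounded up to 38. Then 38 / 0.95 = 40. The stated 40 per group reproduces. With 38 evaluable per arm the power is 80.9% by the normal approximation and 79.9% by the t-test. No covariate enters this formula.

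**2. What the adjustment is worth.** The baseline to follow-up correlation r is not given, so 0.3 to 0.7 is assumed. Residual SD = 20 × √(1 − r²), and power = Φ(13 / (SD × √(2/38)) − 1.96).

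| r | Residual SD | ANCOVA power |
|---|---|---|
| 0.3 | 19.08 | 84.4% |
| 0.5 | 17.32 | 90.5% |
| 0.7 | 14.28 | 97.8% |

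An unadjusted rank test on normal follow-up scores has efficiency 0.955, so 38 × 0.955 = 36.3 effective per arm and about 79.1% power. This compares two fixed methods. It is not the effect of the rule, which uses the rank test only in some trials.

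**3. Does the gate protect validity?** Simulation: 3,000 runs per setting, 38 per arm, SD 20, correlation 0.5 on the underlying normal scale, Shapiro-Wilk at 0.05 in each arm, Mann-Whitney as fallback, transformation step left out.

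| Outcome shape | Gate leaves ANCOVA | Type I error: ANCOVA / gated | Power for 13: ANCOVA / Mann-Whitney / gated | Mean ANCOVA estimate |
|---|---|---|---|---|
| Normal | about 10% | 5.3% / 5.4% | 89.5% / 78.5% / 88.4% | 13.01 |
| Strong skew (reversed gamma, shape 2) | about 98% | 4.8% / 4.8% | 89.2% / 90.7% / 90.7% | 13.03 |

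The 10% in the first row is what two tests at 5% give by chance: 1 − 0.95² = 9.75%. Under strong skew ANCOVA still holds its error rate and recovers the true 13 points, yet the rule discards it almost every time.

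**4. With a ceiling.** Assumptions: score bounded at 0-100, r from 0.3 to 0.7, 38 per arm, transformation tried before the rank test. ANCOVA type I error stayed at about 4-6%.

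- With 5-9% of the steroid arm at the ceiling, the gated rule lost about 0-4 power points against fixed ANCOVA.
- With 14-20% at the ceiling, it ended in a rank test in 56-90% of trials and lost about 3-16 points.

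Runs without the transformation step, at about 20% ceiling, agree: ANCOVA versus gated power was 82% vs 79%, 88% vs 78% and 96% vs 80% at r = 0.3, 0.5 and 0.7, which are losses of 3, 10 and 16 points.

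**The case against.** The best defence is that the order of methods is declared in advance, the analyst is blinded, and no error rate is damaged. The design does not lean on the adjustment either: a rank test keeps about 78-79% power, close to the planned 80%, and under strong skew it slightly beats ANCOVA. The non-parametric test is unnamed, and naming it is something an article may leave to its analysis plan. A rank ANCOVA or a rank test on change scores would keep some adjustment. All of this stands. It limits the harm to scale, interpretability, consistency and possible precision. It does not give the gate a purpose, and the rule itself is stated in the article rather than left open.

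A reader might go further and infer that the 4.0 mm eligibility threshold makes failure likely for thickness. The documents do not support that. The threshold truncates thickness at entry, and the outcome is thickness at follow-up. Simulations at n = 80 used a measurement SD of 0.216 mm, from the stated limits of agreement: (0.5 + 0.7) / (2 × 1.96) / √2. They also assumed an SD of true change of 0.5-1.0 mm. Normality was rejected for baseline thickness in about 9-82% of trials, for follow-up thickness in about 4-34% (mostly under 16%), and for change scores in about 4-6%.

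A reader might also take a pain-score ceiling as given. The article states neither the range nor the direction of the FHSQ pain score, so any ceiling is an assumption.

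**Conclusion.** The point holds as a criticism of a stated decision rule. The gate tests the wrong object and adds no validity at about 38-40 per arm. It can remove the original scale from either primary result, can remove the baseline adjustment, and can split methods across visits. The 13-point benchmark is affected for FHSQ pain only.

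The power cost is uncertain. It runs from nothing to about 16 percentage points over the ranges assumed for ceiling and correlation, and the documents fix neither. Three stronger conclusions should not be drawn: that type I error is inflated, that the stated 80% power fails, or that loss of adjustment is certain. The gap between 97.8% and 79.1% at r = 0.7 should likewise not be quoted as the rule's effect, because it sets always-ANCOVA against always-rank.

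**What to change.** Replace the normality rule with a fixed primary method: every continuous outcome, at every follow-up, is analysed by ANCOVA on its original scale with its baseline value as covariate, whatever a normality test shows. Report bootstrap or heteroscedasticity-robust (HC3) confidence intervals where the software allows. Inspect residuals as a check that does not change the primary method. Keep a transformed or rank-based analysis, preferably baseline-adjusted, as a named sensitivity analysis.

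The cost is about two sentences of text and a little more analysis work. The sample size stays at 40 per group. Robust errors cost about 1 power point: in simulations with a moderate ceiling and 38 per arm, power went from 80.8% to 79.8%, 88.4% to 87.5% and 96.7% to 96.4% at r = 0.3, 0.5 and 0.7. Under strong skew the fixed ANCOVA may be slightly less powerful than a rank test (89.2% against 90.7% above).

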Screening of applicants according to these criteria will occur by a preliminary telephone interview, followed by clinical examination at the initial visit. After a detailed explanation of the study protocol, eligible applicants will be invited to participate in the trial. However, prior to enrolment, all applicants will be assessed for competence to give consent by use of the Evaluation to Sign Consent (ESC) tool [29]. The ESC is specifically designed for use in clinical research and has been shown to have good inter-rater reliability (Pearson *r *= 0.81) [30]. A range of descriptive characteristics will also be collected at the initial visit after enrolment (Table 1). Participants will then be scheduled to attend a second appointment (approximately one week later) where baseline measurements will be taken and the trial intervention performed (Figure 1).

**Table 1 T1:** Descriptive characteristics

Age
Sex
Height
Weight
Body Mass Index (BMI)
Duration of symptoms
Previous and current treatments

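### Baseline adjustment is stated only for normally distributed continuous outcomes; analgesic use probably falls under a non-parametric rule that makes no stated use of pre-injection values, which may cost precision

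*Protocol article*

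**What the plan says.** The Secondary outcomes section lists the outcome and its time points: "Secondary outcomes will be function, use of oral analgesic medication, and 'first-step' pain at 4, 8 and 12 weeks". It adds that "Use of oral analgesic medication (including paracetamol, aspirin, opioids and non-steroidal anti-inflammatory drugs) will be recorded at each visit". It does not say whether use will be coded as yes/no, as an ordered amount or as a dose count.

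Information from before the injection is planned. Table 1, under Setting and eligibility criteria, includes "Previous and current treatments" at the initial visit. The second appointment is the one "where baseline measurements will be taken and the trial intervention performed". The Data analysis section also replaces missing follow-up values with the baseline value, which presupposes that a baseline value exists.

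That section then sets three rules:

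- "Continuous outcomes with a normal distribution will be analysed using a linear regression technique with baseline measurements adjusted for by the analysis of covariance model".
- For continuous data that resist transformation, "if data is still not normally distributed after transformation, non-parametric statistical tests will be used".
- For data that are not continuous, the rule is as follows: "Other data (nominal or ordinal) will be analysed using appropriate non-parametric statistical tests".

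Only the first mentions baseline.

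**The concern.** Whether someone takes painkillers at week 4, 8 or 12 may depend heavily on whether they took them before the injection. If so, a comparison that leaves earlier use out carries avoidable noise, and any chance difference between the arms at baseline stays in the estimate. The protocol itself recognises, under Sample size, that covariate analysis adds precision, and it uses that for its normally distributed continuous outcomes. The rule for nominal and ordinal data does not extend the same benefit, although the data needed are already to be collected.

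At stake is the precision of one secondary comparison. Readers will also look at analgesic use when they interpret the pain result, because unequal use between arms can mask or mimic a difference in pain.

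**Working it through.** **The plan's own figure.** The only size calculation concerns FHSQ pain: difference 13, SD 20, alpha 0.05 (taken as two-sided), power 80%, loss 5%.

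n per arm = 2 × (1.960 + 0.842)² × 20² / 13² = 2 × 7.85 × 400 / 169 = 37.2, rounded up to 38. Allowing for loss, 38 / 0.95 = 40 per arm, 80 in total. The stated figure reproduces. It has no bearing on analgesic use, for which the protocol gives no rates, scale or baseline correlation. Everything below therefore rests on assumed inputs.

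**Chance imbalance.** With 40 per arm and baseline use p, the SD of the between-arm difference is √(2p(1−p)/40). At p = 0.45 this is √(2 × 0.45 × 0.55 / 40) = 0.111, or 11 percentage points. For p between 30% and 50%, the normal approximation gives a probability of about 33% to 37% for a difference of at least 10 points, and about 14% to 18% for at least 15 points. This is ordinary randomisation at this sample size.

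**Power, first set of assumptions.** Yes/no outcome, 40 per arm, 45% baseline use. The log-odds of later use = intercept + b × baseline use + treatment effect, with treatment log-odds −1.4 (odds ratio about 0.25) and intercepts from −1 to 0. Simulated trials compare a Pearson chi-square test with a Cochran-Mantel-Haenszel (CMH) test stratified by baseline use.

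| Baseline log-odds b | Change in power from adjusting |
|---|---|
| 0 to 1.5 | about −1 to +4 points |
| 2.5 (odds ratio about 12) | about +11 to +12 points |

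At b = 2.5 and intercept −1, power is about 59% unadjusted and 71% stratified. With a weaker treatment effect (log-odds −0.7), the gain at b = 2.5 is only about 4 to 5 points, and both tests have power of about 25% or less.

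**Power, second set of assumptions.** Binary use derived from correlated normal variables, 38 evaluable per arm, 50% use at baseline and in the control arm at follow-up. Phi is the correlation between baseline and follow-up use.

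| Phi | 20% use in treated arm: chi-square vs CMH | 25% use in treated arm: chi-square vs CMH |
|---|---|---|
| 0 | 80% vs 79% | 62% vs 62% |
| 0.33 | 80% vs 83% | 62% vs 67% |
| 0.49 | 80% vs 88% | 62% vs 72% |
| 0.71 | 80% vs 95% | 62% vs 85% |

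The two sets agree in pattern. There is nothing to gain when earlier use does not predict later use, a few points at a moderate association, and ten or more once the association is strong.

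**Validity.** With no treatment effect (40% use in both arms), both tests reject in about 5% of trials at every correlation.

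**The case against.** The strongest reply is that the protocol does not say what a critical reader might infer from it. A reader might conclude that the analgesic comparison will be unadjusted and will disregard earlier use. The text names no test for this outcome and does not rule out using baseline. A CMH test stratified by baseline, a van Elteren test and a rank-based covariance analysis are all non-parametric and all fit the wording. The power gain shown above was itself obtained with a stratified CMH test, so it is available within the stated rule. The assignment of analgesic use to this rule is also inferred: a dose count that was normal, or could be made so, would receive the covariance analysis. Finally, the choice of test for a secondary outcome is commonly left to an analysis plan.

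Most of this stands, and it limits the point to what is and is not stated. Two things remain. The protocol does choose a class of method for these data, and the tests most commonly used from that class carry no baseline term. And a dose count with many zeros could well stay non-normal after transformation, in which case it too would go to a non-parametric test with no stated baseline term.

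A reader might also infer that these data would yield only a p-value. The section names tests but does not restrict what is reported, so the documents do not support that.

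**Conclusion.** The point holds as an improvement available at no real cost, not as an error. Baseline adjustment is stated only for normally distributed continuous outcomes, and the rule that probably governs analgesic use makes no stated use of pre-injection values.

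The size cannot be derived from the documents. On the first set of assumptions the power change runs from about −1 to +4 points for a weak to moderate link with earlier use, to about 11 to 12 points for a strong one. The second set spans about −1 to +23 points as phi goes from 0 to 0.71. No single figure should be quoted without the range, and the range includes no gain.

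It would be tempting to call the comparison biased because the arms may differ at baseline. That does not follow. An unadjusted comparison in a randomised trial is valid, its type I error stays at about 5%, and its sampling distribution already allows for chance imbalance. What is lost is efficiency, on one secondary outcome. The analysis of the primary outcomes and the sample size of 80 are unaffected.

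**What to change.** In the Data analysis section, state the form in which analgesic use will be analysed (yes/no or ordered amount). State also that it will be compared between arms by logistic or proportional-odds regression, with arm and pre-injection use as covariates. If a non-parametric method is preferred, name a test stratified by pre-injection use: CMH for a binary form, van Elteren for an ordered one. Say which visit supplies the pre-injection value, and report the adjusted effect with a 95% CI.

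The cost is a sentence or two. The data are already to be collected at each visit, and neither the visit schedule nor the sample size changes. An odds ratio from the regression is conditional on earlier use, so it should be labelled as adjusted and not set directly against an unadjusted one.
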